6.2 Visit content and requirements

6.2.1 Baseline characteristics of subjects

6.2.1.1 Demographic data and past medical history

Prior history and demographic data of the subjects should be collected as far as possible before enrollment, confirmed to meet inclusion/exclusion criteria, and the omitted or corrected prior history and demographic data found in the whole study process should also be recorded in the subsequent original data.

1. Demographic data: date of birth, gender, ethnicity and occupation;
2. Height, weight and ECOG score (see Appendix II);
3. Previous history:

- Histopathological diagnosis: pathological diagnosis, date of first diagnosis, pathological tissue acquisition method, histopathological grade;
- Clinical diagnosis before enrollment: Lugano stage (see Annex V), Follicular Lymphoma International Prognostic Index 2 (FLIPI-2) (see Annex VI);
- History of surgical treatment: date, surgical indications, description of surgical treatment;
- History of stem cell transplantation: date, type of transplantation, source of stem cells, description of transplantation, whether recurrence or progression and its date;
- History of chemical/targeted/immunotherapy (including adjuvant therapy): name of drug used, dose, best response, medication cycle, start and end time, whether treatment failure or progression and its date;
- History of radiotherapy: start and stop time, radiotherapy site, total dose, best efficacy.

1. Other past medical history:

- Disease history: Disease history within 5 years prior to signing ICF, such as diabetes and hypertension, should be recorded;
- Allergic history: allergen;
- Smoking history;
- Concomitant disease And abnormalities : Clinically significant abnormalities that are ongoing at Screening will be considered concurrent medical conditions or symptoms and will be observed continuously during the study after Investigator's judgment/diagnosis.

6.2.1.2 Vital Signs

Baseline vital signs should be completed within 3 days prior to the first dose. Pulse rate, blood pressure, body temperature and respiration. All vital signs should be measured with the subject at rest. If body temperature is measured more than twice in a day, the highest measurement should be recorded.

6.2.1.3 Physical examination

Complete physical examination at baseline should be completed within 7 days prior to the first dose. Including: general appearance examination, skin system, head (head, eyes, ears, nose and oral cavity), neck, lymph nodes, chest (lungs, heart, etc.), abdomen (liver and gallbladder, spleen, etc.), limb examination and nervous system examination. Targeted physical examinations were limited to systems that were clinically relevant (ie, cardiovascular, respiratory, lymph node, liver, and spleen) and associated with clinical signs/symptoms. In the event of clinical suspicion of disease progression at any time, a prompt physical examination will be required rather than waiting for the next scheduled imaging assessment.

6.2.1.4 B Symptom assessment

Baseline B symptom assessment should be completed within 7 days prior to the first dose. B symptom assessment content: unexplained weight loss of 10% (within 6 months before diagnosis), fever > 38℃ and rule out other causes of fever, night sweats (heavy sweating at night, need to change clothes and bedding).

6.2.2 Laboratory Tests

The baseline laboratory test results (the results of infection and immune indicators test, CMV-DNA test, epidemiology, blood gas analysis and pulmonary function monitoring were acceptable) 7 months before the first dose were beyond the acceptable time range. The test should be performed again to meet the requirements of the clinical study.

Table 15 Contents of laboratory tests

| Inspection category | Inspection item |
| --- | --- |
| Blood routine | White blood cell count (WBC), neutrophil count (ANC), lymphocyte count (LYM), red blood cell count (RBC), hemoglobin (HB), platelet count (PLT) |
| Blood biochemistry | Liver function: total bilirubin (TBIL), direct bilirubin (DBIL), alanine aminotransferase (ALT), aspartate aminotransferase (AST), alkaline phosphatase (ALP), serum albumin (ALB), serum total protein (TP), γ-glutamyltransferase (GGT), lactate dehydrogenase (LDH);  Renal function: blood urea nitrogen (BUN)/urea (UREA), creatinine (Cr); fasting blood glucose (GLU); uric acid (UA);  Electrolytes: potassium (K), sodium (Na), chloride (Cl), calcium (Ca), magnesium (Mg),  Inorganic phosphorus (P);  Four items of blood lipids: total cholesterol (TC), triglyceride (TG), high-density lipoprotein (HDL), low-density lipoprotein (LDL) |
| Glycosylated hemoglobin | Glycosylated hemoglobin (HbAlc) |
| Infection and Immunity  Indicator inspection | Infection indicators: procalcitonin (PCT) and C-reactive protein (CRP)  Immune parameters: CD4 + T lymphocyte count, CD8 + T lymphocyte count, CD4 +/CD8 + ratio |
| CMV-DNA  Inspection | Serum CMV-DNA levels (checked by CMV PCR) |
| Urine routine | Urine protein (PRO), urine glucose (GLU), urine red blood cell (RBC), urine white blood cell (WBC), urine ketone (KET), urine pH (PH) |
| Stool routine | Fecal white blood cells (WBC), fecal red blood cells (RBC), fecal occult blood (OB) |
| Β2 microglobulin | Β2 microglobulin (β2-MG) |
| Amylase | Serum Amylase (AMS) |
| Lipase | Serum Lipase (LPS) |
| Coagulation function | International normalized ratio (INR), prothrombin time (PT), activated partial thromboplastin time (APTT), thrombin time (TT), fibrinogen (FBG), D-dimer |
| Pregnancy test | Urine or serum pregnancy test, only for women of childbearing potential |
| Epidemiology | Anti-HIV ;  Hepatitis B surface antigen (HbsAg) (hepatitis B virus deoxyribonucleic acid HBV-DNA is added when positive), hepatitis B surface antibody (HBsAb), hepatitis B e antigen (HBeAg), hepatitis B e antibody (HBeAb) and hepatitis B core antibody (HBcAb);  Hepatitis C Antibody (Anti-HCV) |
| Finger oxygen monitoring | Saturation (SaO2) |
| Blood gas analysis | Saturation (SaO2), partial pressure of oxygen (PaO2), partial pressure of carbon dioxide (PaCO2), pH, oxygenation index (P/F) |
| Pulmonary function monitoring | Forced expiratory volume in the first second (absolute value of FEV1), pulmonary diffusion capacity (DLCO) |

Note: Laboratory tests specified in the protocol should be performed in our center if there are no special circumstances. If our center has no examination conditions, it is recommended to perform the test in a fixed outside hospital.

6.2.3 Cardiac function test

12-ECG: The ECG report and paper should be traceable 7 times before the first dose is administered during the screening period. The name of the subject and examination time should be clearly recorded by the thermosensitive spectrum, and the spectrum measured by the bedside ECG should be photocopied for reference only and not included in the statistical analysis.

Echocardiography: 14 results before the first dose are accepted in the screening period, and the examination results should include at least the score.

If chest pain, palpitation and other symptoms occur, it is recommended to additionally check echocardiography and myocardial enzymes (CK, CK-MB), troponin (cTnT, cTnI).

6.2.4 Imaging examination

**Examined site: The screening period must include brain, neck, chest, abdomen and pelvis; the subsequent cycles should include neck, chest, abdomen and pelvis at least. The sites with other suspicious lesions should also be examined as clinically indicated.**

**Examination methods: CT/MRI (CT is the first choice for neck, chest, abdomen and pelvis, MRI is the first choice for brain, and enhancement is required for all), whole-body PET-CT.**

**Requirements for examination: The examination during the treatment period should be performed under the same conditions as the screening period. For subjects enrolled without PD, PFS should be collected after enrollment, i.e., they should continue to return to the hospital for imaging examination as scheduled until PD (or initiation of other systemic anti-tumor treatment or death, whichever occurs first). The examination specification should refer to the 2014 edition of Lugano evaluation criteria to ensure that the efficacy can be reasonably assessed.**

**Time requirement: Imaging time does not change due to dose regimen modification. CT/MRI/PET-CT results meeting the study requirements 28 days before the first dose in the screening period.**

The specific time of CT/MRI examination:

① Screening period (within 28 days prior to the first dose);

② During treatment, the first dose is taken as the time point until disease progression (or initiation of other systemic anti-tumor therapy or death, whichever occurs first); CT/MRI assessment is performed every 8 weeks in the first 48 weeks ( time point until disease progression (or initiation of other systemic anti-tu

③ CT/MRI should be performed at the end of treatment visit (VEOT) regardless of confirmation of enrollment for any reason (if CT/MRI was performed 28 days before VEOT, it is not necessary to repeat at VEOT).

The specific time of PET-CT examination is:

① Screening period (within 28 days prior to the first dose);

② When CR was assessed by CT/MRI, complete remission (CR) was confirmed using PET-CT within 7 days after assessment;

③ PET-CT was performed on Day 112 (i.e., Week 16), Day 224 (i.e., Week 32), and Day 336 (i.e., Week 48) after the first dose (± 7 days), followed by PET-CT every 32 weeks (± 7 days), that is, at Weeks 80 and 112... PET-CT evaluation was performed at the same time point; when CT/MRI evaluation was CR and PET-CT confirmation was performed at 7 weeks, the latest 8 times of PET-CT examination plan could be exempted, and subsequent PET-CT was performed as planned normally (for example, when CT/MRI evaluation at Week 24 was CR and PET-CT confirmation was performed at 7 weeks, PET-CT at Week 32 was not performed);

④ PET-CT should be performed at the end of treatment visit (VEOT) regardless of confirmation of enrollment for any reason (if PET-CT was performed 56 days before VEOT, it is not necessary to repeat at VEOT).

**Record requirements: Radiographers should save the uncompressed images in DICOM format (film, JPG, BMP and other image formats are not acceptable) in the preferred media (CD/DVD) of the study site, and retain a copy of image data at the study site for review by regulatory authorities.**

9 SAFETY ASSESSMENTS

9.1 Adverse Events

An adverse event (AE) is any untoward medical occurrence in a clinical investigation subject administered a pharmaceutical product and which is manifested by symptoms, signs, disease, or laboratory abnormalities and which does not necessarily have a causal relationship with this treatment.

Investigators should record in detail any adverse events occurring during the medication of subjects. Recording of adverse events includes: description of adverse events and all related symptoms, onset time, severity, duration, measures taken, final outcome and outcome.

9.2 Evaluation of Adverse Events

The nature and severity of adverse events were evaluated according to the National Cancer Institute Common Terminology Criteria for Adverse Events [NCI-CTC AE 5.0].

9.3 Adverse events of records

During the AE reporting period stipulated in the protocol, the investigator is responsible for collecting all AEs (including SAEs) and recording them in the eCRF. When recording AEs, the investigator should use correct and standardized medical terminology to avoid colloquialisms and abbreviations. The start time of AE, the highest degree of NCI-CTC AE 5.0 grade, the end time, the correlation with the study drug, the influence with the study, the presence or absence of concomitant treatment and the recovery should be recorded.

Diagnosis vs Symptoms and Signs

If a diagnosis is already present, the diagnosis should be recorded in the eCRF rather than individual signs and symptoms (e.g., record liver failure rather than jaundice, elevated transaminases, and flapping tremor). However, if signs and symptoms cannot be attributed to a single diagnosis at the time of reporting, each individual event should be recorded as an AE on the eCRF. If a diagnosis is later established, it should be updated on the eCRF to record the diagnosis.

Adverse Events Secondary to Other Events

In general, AEs secondary to other events (e.g., caused by other events or clinical sequelae) should have their primary event recorded, unless the secondary event is more severe or an SAE. However, secondary events with significant clinical significance should be recorded as independent AEs in eCRF if they occur at a different time from the primary event; if the relationship between the events is unclear, the primary event and secondary event should be recorded separately.

Continuous, intermittent or isolated adverse events (frequency of adverse events)

Continuous AE refers to an AE persisting during the whole process without remission, for example, upper respiratory tract infection lasting for 5 days. Only one AE should be recorded in the eCRF. For severity assessment, the most severe severity throughout the event should be recorded.

Intermittent AEs are AEs that change or are relieved in symptoms, signs or laboratory parameters during the whole process, but do not have clinically significant outcomes, such as nausea and vomiting that last for many days, during which there is relative remission; subjects with hypertension have a relatively continuous course of hypertension despite intermittent remission in multiple blood pressure tests. Such AEs may only be recorded in one eCRF. The most severe severity over the course of the event should be recorded during the intensity assessment.

A separate AE (Single AE) is defined as an AE that can logically only occur alone, or that occurs only once during the trial, for example, an accident in which a subject falls while taking a drug; or vomiting that a subject only experiences once during the trial. Only one such AE should be recorded on the eCRF.

It should be noted that if the above AE has recovered from significant clinical significance, but the same AE occurs later and the latter is considered to have no continuous course with the former, the occurrence of the event should be recorded separately in the eCRF.

Laboratory abnormalities or vital signs

All laboratory test results may be recorded on the laboratory results page of the eCRF. Not all laboratory abnormalities/vital sign abnormalities should be recorded as AEs, and it is the responsibility of the investigator to review all laboratory abnormalities and abnormal vital signs and make medical judgment as to whether they should be recorded as AEs. Any of the above abnormalities with significant clinical significance, for example, one or more of the following conditions should be recorded as AE:

- Accompanying clinical symptoms
- Results in a change in study medication (e.g., dose modification, temporary or permanent discontinuation)
- Requires medical intervention or change in concomitant therapy (e.g., increase, suspension, discontinuation, or other change in concomitant medication, therapy, or treatment)
- Clinically significant as judged by the investigator

If a clinically significant laboratory abnormality or vital sign abnormality is a sign of a disease or syndrome (e.g., increased ALT/AST and blood bilirubin due to hepatic impairment), only the diagnosis (i.e., hepatic impairment) should be recorded on the Adverse Event form of the eCRF. Otherwise, laboratory abnormalities or vital sign abnormalities should be recorded on the Adverse Event form of the eCRF and indicate whether the test value is above or below the normal range. If there are standard clinical terms corresponding to the laboratory abnormalities or vital sign abnormalities, the clinical term should be recorded in the eCRF (e.g., increased blood potassium to 7.0 mmol/L should be recorded as"hyperkalemia").

Death

When recording a death event, if there is an AE leading to death, the AE leading to death should be recorded in the eCRF as an SAE using a single medical concept and the event should be reported as an SAE; if the cause of death is unknown, "unexplained death" should be recorded in the AE form of the eCRF and reported as an SAE as "unexplained death", followed by further investigation into the exact cause of death, and the record and SAE report should be updated after the cause of death is known.

Pre-existing medical conditions

The preexisting symptoms/signs a subject has already presented during the screening period of the trial will be recorded as AEs only when there is worsening in severity, frequency, or nature (except for worsening of the medical condition under study) after entry into the trial. Changes from the previous state should be reflected in the records, such as "increased frequency of headache", "aggravated hypertension", etc.

Hospitalization, prolonged hospitalization

The following situations result in hospitalization or prolonged hospitalization, which should not be reported as SAE:

- Planned hospitalization or prolongation of hospitalization as required by the protocol (e.g., for dosing, efficacy assessment, etc.);
- Hospitalization for a medical condition that was present and unchanged prior to study participation, such as an elective surgery or treatment scheduled before study participation, or an inpatient hospitalization for surgery or treatment scheduled after study participation, is not considered an adverse event. However, if the condition of the existing disease worsens during the study (e.g., surgery or treatment should be performed earlier than originally planned), hospitalization for surgery or treatment is required due to the deterioration of the disease, and the deterioration of the condition will be considered as an SAE.

Surgery

If the condition being treated by the procedure is known, the condition should be recorded as the AE rather than the procedure itself (e.g., if the subject has undergone inguinal hernia repair, an"inguinal hernia"should be recorded instead of"inguinal hernia repair"); however, if the reason for the procedure is unclear, the procedure may be recorded as the AE (e.g., if the subject has undergone abdominal exploration, an"abdominal exploration"may be recorded as the AE).

Pregnancy

If a female subject or female partner of a male subject becomes pregnant during the study, the investigator should be notified immediately. The investigator should report the completed pregnancy report form to the sponsor according to the SAE reporting procedure within 24 hours after learning of the pregnancy. Female subjects who become pregnant should discontinue study drug immediately. The investigator should discuss with the subject about the risks of continued pregnancy and possible effects on the fetus. Subjects should be monitored until the end of pregnancy. Pregnancies that occur within 28 days of study drug administration should be reported to the investigator.

Whether artificial or spontaneous abortion should be recorded and reported as SAE. Any congenital abnormality or birth defect of the infant born by female subject or female partner of male subject who has taken study drug should be recorded and reported as SAE.

Disease progression

An AE was to be considered if the occurrence of an event was clearly consistent with the expected pattern of progression of the primary tumor. Hospitalization solely due to progression of this disease is also considered an SAE. If symptoms cannot be confirmed to be completely caused by disease progression, or it is inconsistent with the expected pattern of tumor progression, relevant clinical symptoms may be recorded as AE, which conforms to SAE reportable SAE.

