9.6 Serious Adverse Events

Any untoward medical occurrence that results in death, is life-threatening, results in persistent or significant disability or incapacity, requires inpatient hospitalization or prolongation of existing hospitalization, or is a congenital anomaly or birth defect after the subject has received investigational product. If a patient or his/her spouse becomes pregnant, it shall be reported to the relevant unit as a serious adverse event.

Disease progression, including signs and symptoms of progression, should not be reported as a serious adverse event, but death due to disease progression should be reported as a serious adverse event if it occurs during the trial or safety reporting period. Hospitalization for signs and symptoms of disease progression should not be reported as a serious adverse event. During the trial or safety reporting period, if the final outcome of cancer is death, the event that led to death must be reported as a serious adverse event.

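### Section 9.3 makes clear progression events AEs and progression admissions SAEs, against section 9.6 and partly against 9.3 itself, so safety summaries depend on which rule a site follows

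*Protocol*

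**What the plan says.** Three places in the protocol govern what is recorded when lymphoma progresses.

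- **Section 9.3, Disease progression.** The first sentence reads "An AE was to be considered if the occurrence of an event was clearly consistent with the expected pattern of progression" of the primary tumour. The second reads "Hospitalization solely due to progression of this disease is also considered an SAE". The third covers the uncertain case: "If symptoms cannot be confirmed to be completely caused by disease progression, or it is inconsistent with the expected pattern of tumor progression", then "relevant clinical symptoms may be recorded as AE", with SAE reporting where a criterion is met.
- **Section 9.3, Pre-existing medical conditions.** Symptoms or signs already present at screening become AEs only if they worsen in severity, frequency or nature, "except for worsening of the medical condition under study".
- **Section 9.6.** "Disease progression, including signs and symptoms of progression, should not be reported as a serious adverse event", and "Hospitalization for signs and symptoms of disease progression should not be reported as a serious adverse event". Death due to progression during the trial or the safety reporting period is still an SAE.

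Behind these stands the general duty at the start of 9.3: "the investigator is responsible for collecting all AEs (including SAEs) and recording them in the eCRF". Section 9.1 defines an AE without requiring a causal link to treatment. Section 11.5.2 counts as a TEAE any AE that appears or worsens after study drug is used. It summarises all TEAEs, Grade 3 and higher TEAEs and SAEs, with separate summaries of drug-related events.

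**The concern.** In the disease-progression paragraph, events plainly due to lymphoma are AEs. Symptoms whose cause is open, where a drug effect remains possible, get softer wording. The third sentence reads naturally only as an exception to a rule that leaves progression events out, and the first sentence does not state such a rule. Section 9.6 and part of 9.3 then point the other way.

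Treatment continues until progression or intolerance (3.1), so symptoms of progression will tend to arise on treatment or near its end, within AE collection. Safety is a secondary endpoint (2.2). In a single-arm trial no comparator would show that part of a TEAE or SAE rate is disease. If some sites follow the disease-progression paragraph and others follow 9.6 and the pre-existing-conditions rule, the pooled rates mix two definitions.

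**Working it through.** No alpha, power, rate or sample size enters this point, so there is nothing to compute. The check is to apply each rule to the same situation.

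| Situation | 9.3, Disease progression | Other rule | Result |
| --- | --- | --- | --- |
| Admission solely for progression: SAE? | Yes | 9.6: no | Direct contradiction |
| Signs or symptoms of progression meeting an SAE criterion, short of death: SAE? | They are AEs, with no exemption from SAE reporting | 9.6: no | Contradiction |
| Lymphoma symptom present at screening that worsens at progression: AE? | Yes | 9.3, Pre-existing medical conditions: no | Contradiction |
| New symptom clearly due to progression: AE? | Yes | 9.1 and the opening of 9.3: an AE whatever its cause | No contradiction at AE level |
| Symptom not confirmed as entirely due to progression: AE? | *May* be recorded | Opening of 9.3: all AEs are recorded | Contradiction only if *may* means optional |
| Death due to progression: SAE? | Not addressed in this paragraph | 9.6: yes | No contradiction |

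**Is the first sentence damaged text?** The first two sentences are complete and both affirmative; the second continues the first by saying that admission is *also* an SAE. They show none of the garbling found elsewhere in the file.

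**Effect on the summaries.** Take one post-dose event clearly due to progression.

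1. Under the disease-progression paragraph it is an AE. Because 11.5.2 makes no exception for progression, it is also a TEAE. It enters the Grade 3 or higher table if its grade qualifies, and the SAE table if the subject is admitted.
2. Under 9.6 the same admission adds nothing to the SAE table.
3. Under the pre-existing-conditions rule, if the symptom was present at screening, it adds nothing to any AE table.

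For such events, the disease-progression paragraph can therefore only raise the all-cause TEAE, Grade 3 or higher TEAE and SAE counts relative to the other two rules, or leave them equal.

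**Size.** This would need the number of subjects with symptomatic progression in the AE reporting period, the share whose symptoms were present at screening, the share admitted, the share already counted for another event, and the split of sites between the rules. The protocol gives none of these.

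**Less exposed outputs.** Adverse reactions count only events judged definitely, probably or possibly related (9.5), and 11.5.2 tabulates drug-related TEAEs and SAEs separately. Events clearly due to lymphoma should fall out of both. The primary ORR analysis uses no AE data.

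**The case against.** **A negation was probably lost in translation.** The English text has obvious translation errors elsewhere, and the third sentence fits an original that excluded progression events. Sites may be working from a correct source text. That is plausible and lowers confidence that the defect is operative. It cannot be shown from this document, and it would explain the stated rule without removing it. It does make the source-language text the first thing to check.

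**Recording progression symptoms as AEs is consistent with the general definition.** This stands for new symptoms. A reader might infer that the pre-existing-conditions rule removes every progression symptom from the AE form. It does not: it covers only symptoms already present at screening, and new pain, effusion or fever at progression lies outside it. The conflict inside 9.3 is correspondingly narrower, and the firmest conflict is with 9.6.

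**The word *may* is used loosely.** Section 9.3 also says laboratory results *may* be recorded on their eCRF page, where an instruction is evidently meant. A reader might infer that possible drug events will be lost. The documents do not support that as an outcome: 9.1 and the opening of 9.3 still require all AEs, whatever their cause. The optional wording is a risk to close.

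**The effect on headline rates may be modest.** In phase I, hyperglycaemia alone affected 36 of 60 subjects (60.0%) and diarrhea 23 of 60 (38.3%). Many subjects would already count in the any-TEAE rate, so added progression symptoms do not translate one for one into incidence. Section 4.5 also lists progression and adverse events as separate withdrawal reasons, which limits mixing in discontinuation figures. Both points stand, and they argue against putting a number of subjects on the effect.

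**Conclusion.** The point holds as a contradiction in the recording rules. Section 9.3 and section 9.6 give opposite answers on whether hospitalization for progression is an SAE. Section 9.3 also disagrees with itself on worsening lymphoma symptoms that were present at screening. If *may* is read as optional, it further conflicts with the duty to record all AEs.

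The direction is clear: following the disease-progression paragraph raises the all-cause TEAE, Grade 3 or higher TEAE and SAE summaries compared with following the other two rules. This assumes that sites follow the English text as printed and that some progression in the AE reporting period is symptomatic. The size cannot be derived. Drug-related summaries are less exposed, and the ORR test is untouched. It should be corrected before database lock, but it does not threaten the trial's primary conclusion.

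**What to change.** 1. Check the disease-progression paragraph of 9.3 against the source-language protocol.
2. Reconcile that paragraph, the pre-existing-conditions rule in 9.3 and section 9.6 into one rule. It should say whether an event clearly due to progression is an AE, covering new symptoms and those present at screening separately, and whether admission for it is an SAE.
3. In the same rule, state that a symptom not confirmed as entirely due to progression must be recorded as an AE, and reported as an SAE if it meets a criterion.
4. Send a site memo, and before database lock query AE and SAE records around progression so that all sites are brought to the one rule.

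The cost is one reconciled rule in an amendment, a memo and a limited round of queries, with no new assessments. Timing matters because section 10.5 says that, in principle, the database is not reopened after lock.
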